### Outcome measures

#### Primary outcome measure

*Sensitivity*—the proportion of women with endometrial cancer who test positive by cytology (true positive rate) and *specificity*—the proportion of women who do not have endometrial cancer who test negative by cytology (true negative rate). The accuracy of cytology (index test) will be defined by the results of standard endometrial cancer diagnostic tests (reference standard, figure 2).

### Secondary outcome measures

NPV—the proportion of women with a negative test who do not have endometrial cancer and *positive predictive value*—the proportion of women with a positive test who have endometrial cancer.False positive/negative rates (and clinical scenarios associated with these).Overall diagnostic accuracy of cytology for endometrial cancer detection.Clinical performance of cytology for the detection of endometrial, cervical or bladder cancer.Clinical performance of cytology for the detection of any pelvic cancer.Test acceptability (short questionnaire to compare acceptability of urogenital sampling with standard diagnostic tests in a proportion of participants, eg, 5%–10%).

### Vaginal or urine cytology

Sensitivity and specificity of vaginal or urine cytology alone for endometrial cancer detection.NPV, positive predictive value and false positive/negative rates of vaginal or urine cytology alone for endometrial cancer detection.Overall diagnostic accuracy of vaginal or urine cytology alone for endometrial cancer detection.Clinical performance of vaginal or urine cytology alone for the detection of endometrial, cervical or bladder cancer.Clinical performance of vaginal or urine cytology alone for the detection of any pelvic cancer.

### Handling of discordant results

The accuracy of urogenital cytology will be measured against standard diagnostic tests for endometrial cancer. Concordance of cytology results between observers will be recorded, but primary analysis will consider ‘ACUS’, ‘suspicious’, ‘adenocarcinoma’ or ‘malignant (others)’ cytology results by consensus opinion to be a positive result. ‘False negative’ results, where standard tests identify endometrial cancer but urogenital cytology does not, will be reviewed to identify possible contributing factors (patient factors, tumour factors or test errors). Subject to ongoing consent, women will be resampled before they undergo hysterectomy, to determine whether repeat sampling is helpful for missed cases. This will be possible because cytology results will be reported prospectively, in ‘real time’ and on a weekly basis, wherever possible. Cytology review of missed cases will be carried out at a multiheaded microscope by the cytology team. Second±further slides will be prepared and reviewed where sufficient residual sample allows. ‘False positive’ cases, where urogenital cytology is positive but standard tests are not, will be handled carefully. If the diagnostic pathway (figure 2) has not been completed, the responsible clinician will be contacted and asked to consider further tests, for example, hysteroscopy or an MRI scan. If the malignant cells identified by cytology could have originated elsewhere, further tests may be warranted (eg, cystoscopy and colposcopy). Retrospective blinded review of 10% of cases, including test positive, test negative, complex and discrepant cases, will facilitate formal assessment of intraobserver and interobserver variability and whether or not there is evidence for a ‘learning curve’ effect.

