### Sample handling

Urine samples will be tested for haematuria by dipstick. Urine and vaginal samples will be fixed with equal volumes of BD CytoRich Red Preservative (Becton, Dickinson and Company, the USA) to preserve cellular integrity, prevent degradation and inhibit bacterial overgrowth. Samples will be sent to the Manchester Cytology Centre at the Manchester University NHS Foundation Trust (MFT). Samples will be anonymised and labelled with sample type (urine or vaginal fluid) and a unique study identifier (study ID) to prevent accidental unblinding of the cytopathology team. With the exception of whether the participant is taking exogenous hormones, all clinical data will be withheld from the cytology team until consensus results are received. Second urine samples will be fixed with BD CytoRich Red Preservative and stored at 4°C until the first urine sample has undergone cytological assessment. This second sample will undergo cytological review if the first urine sample is inadequate for analysis or post hoc, if the first urine sample is false negative for endometrial cancer detection. Residual samples will be stored in the MFT Biobank for future biomarker discovery work. Samples will be either embedded in agar cell blocks to preserve cellular integrity for future immunocytochemistry or centrifuged to pellet the cellular material. The resulting pellet plus aliquots of the supernatant will be stored at −80°C.

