### Reference standard

The reference standard is histology where endometrial tissue is collected for routine diagnostic and staging purposes. The hysterectomy specimen will be used in preference to the endometrial biopsy, where available within 3 months of endometrial biopsy and where there was no treatment with neoadjuvant chemotherapy or hormone therapy. Histology results will be classified as inadequate, benign, atypical hyperplasia and endometrial cancer (of any histological subtype or grade). For the primary analysis, a histological diagnosis of endometrial cancer will be considered a positive result. We will report overall results as well as a breakdown by histological subtype and stage of disease. Hyperplasia and benign endometrium will be considered a negative result. In secondary analyses, cancers of other pelvic sites (cervix, vagina, uterus, ovary, fallopian tube, bladder, kidney or bowel) will be considered a positive result. We will record cases of atypical hyperplasia and their cytological interpretation. In cases where an endometrial biopsy is not indicated (endometrial thickness <4 mm and/or normal hysteroscopy) or fails (inadequate sample), the reference standard will be discharge from diagnostic workup. Passive clinical follow-up of negative women will ensure missed diagnoses of endometrial cancer are minimised. This will involve monitoring for any subsequent rereferrals to our service. A diagnosis of endometrial cancer within 3 months of initial discharge from diagnostic workup will be considered a positive clinical result.

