### Blinding

In most cases, research samples will be collected prior to routine diagnostic workup, and sample takers will be blinded to participant cancer outcomes. If the proportion of cases is less than 5% at the midpoint of the study, the cohort will be enriched with endometrial cancer diagnoses by recruiting higher-risk women (endometrial thickness >4 mm on TVS) and those with proven endometrial cancer prior to hysterectomy. Care will be taken to collect research samples at least 7 days after any diagnostic uterine instrumentation. The cytology team will always be blinded to the cancer status of participants when performing cytological review of urine and vaginal samples. They will have no access to clinical data or results of routine diagnostic tests. Individual participants will not routinely receive their cytology results.

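### Positive cytology can trigger extra reference tests with no counterpart for negative cytology, which slightly inflates endometrial sensitivity and leaves other pelvic cancers unevenly ascertained

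*Protocol article*

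**What the plan says.** All places are in the Protocol article.

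- **Cytology positive, standard tests negative** (Handling of discordant results): on condition that the pathway of figure 2 is incomplete, "the responsible clinician will be contacted and asked to consider further tests, for example, hysteroscopy or an MRI scan". Where the cells could have another origin, "further tests may be warranted (eg, cystoscopy and colposcopy" are the examples given. Cytology is reported in near real time, so this contact can happen during work-up.
- **No histology** (Reference standard): where biopsy is not indicated or fails, "the reference standard will be discharge from diagnostic workup". Later cancers are picked up by passive follow-up: "This will involve monitoring for any subsequent rereferrals to our service". A later diagnosis counts as reference-positive if it is endometrial cancer made within 3 months of discharge. No such rule is given for other cancers.
- **Other cancers** (Secondary outcome measures): the list includes "Clinical performance of cytology for the detection of any pelvic cancer", and also endometrial, cervical or bladder cancer taken together. The section Vaginal or urine cytology repeats both for each sample type alone. Statistical analyses applies the primary approach to secondary analyses, which means sensitivity, specificity, NPV and PPV with exact intervals.
- **Known false negatives**: the stored second urine is read "post hoc, if the first urine sample is false negative for endometrial cancer detection" (Sample handling). Handling of discordant results adds resampling before hysterectomy, extra slides and a joint microscope review by the cytology team.
- **Blinding**: "The cytology team will always be blinded to the cancer status of participants" when reviewing samples. The strengths and limitations box and Sample handling limit blinding to the period before the consensus result.

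**The concern.** In an accuracy study the reference standard should reach women in the same way whatever their index result. Here a positive index result can add reference tests that a negative one cannot. An occult cancer in a cytology-positive woman may be found and become a true positive. The same cancer in a cytology-negative woman without histology stays a true negative unless she returns to the service within 3 months. This differential verification favours the test, in a study meant to support its use for ruling out cancer.

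It is a larger problem for cancers outside the endometrium. The routine pathway is directed at the endometrium, and the named tests for other organs follow a positive cytology result. Sensitivity and NPV for those cancers would then depend on who was investigated as well as on the test.

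A smaller matter is that the absolute blinding statement does not fit the planned review of cases already known to have been missed.

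**Working it through.** **1. The plan's own figures (Sample size).** Cancers needed for ±7 points at 85%: 1.96² × 0.85 × 0.15 / 0.07² = 99.96. At 5% prevalence, 99.96 / 0.05 = 1999, against about 2000 stated. Negative tests: 0.85 × 1900 + 0.15 × 100 = 1615 + 15 = 1630. NPV = 1615/1630 = 99.08%, Wilson interval 98.5% to 99.4%. These match. False positives would be 0.15 × 1900 = 285, and the women eligible for the extra contact come from this group.

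**2. Routes to a reference diagnosis.**

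| Step | Cytology positive | Cytology negative |
|---|---|---|
| TVS, and biopsy from 4 mm | yes | yes |
| Pathway incomplete | clinician contacted about further tests | no equivalent step |
| Possible non-endometrial source | cystoscopy, colposcopy may follow | no equivalent step |
| After a negative work-up | passive rereferral monitoring | passive rereferral monitoring |
| 3-month rule | endometrial cancer only | endometrial cancer only |

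**3. Effect on endometrial sensitivity.** Let s be true sensitivity, and a₊ and a₋ the shares of cancers ascertained among cytology-positive and cytology-negative women. Then

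observed sensitivity = s·a₊ / (s·a₊ + (1 − s)·a₋).

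The article gives no rate of missed cancers, so the following are assumptions. The standard pathway misses m of 100 cancers. Missed cancers are cytology-positive as often as the others. A share f of the missed cytology-positive ones is found through triggered tests, and none of the cytology-negative ones is found. So a₋ = (100 − m)/100 and a₊ = (100 − m + f·m)/100. Example with s = 85%, m = 10, f = 1: 0.85 / (0.85 + 0.15 × 0.90) = 0.85/0.985 = 86.29%.

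| True s | m = 2 (f = 0.5; 1) | m = 5 (f = 0.5; 1) | m = 10 (f = 0.5; 1) |
|---|---|---|---|
| 75% | 75.19; 75.38 | 75.48; 75.95 | 76.00; 76.92 |
| 80% | 80.16; 80.32 | 80.41; 80.81 | 80.85; 81.63 |
| 85% | 85.13; 85.26 | 85.33; 85.64 | 85.68; 86.29 |

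The excess runs from 0.13 to 1.92 points. With f = 0, meaning triggered diagnoses are set aside, the formula returns s. A with-and-without comparison is therefore informative for sensitivity.

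**4. NPV.** NPV uses cytology-negative women only, so triggered diagnoses cannot move it. It is exposed to the unfound cancers on that side. At s = 85% these number 0.15 × 2 = 0.3 to 0.15 × 10 = 1.5, giving 1615.3/1630 = 99.10% to 1616.5/1630 = 99.17%, against 99.08%.

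**5. Other pelvic cancers.** The same formula applies. If a₋ equals a₊ it returns s; if a₋ is smaller the result exceeds s. The article gives none of s, a₊ or a₋ for these cancers, so the direction follows but the size does not. The outcome is not trivial: three of the seven pilot cancers (cervical, ovarian, bladder) were non-endometrial (Introduction).

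**6. Re-reads and blinding.** The primary analysis uses the consensus result. A case can be called a false negative only after that result has been compared with the reference, so the later reads fall outside the blinded period. If the consensus result stands, their effect on sensitivity is zero. The word *always* in Blinding nevertheless conflicts with a review of cases known to be missed.

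**The case against.** The strongest defence is about scope and size. Endometrial contact with the clinician is limited to women whose pathway is incomplete. Cytology-negative women still have TVS, biopsy from 4 mm and rereferral monitoring. The scenario shifts lie well inside the planned ±7 points. All of this stands as to size. It does not remove the asymmetry, and it offers little for cancers that the endometrial pathway is not designed to find.

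Several stronger readings are tempting, and the article does not support them.

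- *Re-reads inflate sensitivity.* A reader might infer that if 5 to 8 of the 15 expected false negatives turned positive on a second urine or resample, sensitivity would become (85 + 5)/100 = 90% to (85 + 8)/100 = 93%. Nothing prescribes such recoding. The second-urine read is called post hoc, the stated aims are to find reasons for misses and to see whether resampling helps, and no conversion rate is given. A condensed article need not spell out the exclusion.
- *Blinding is broken.* The read that feeds the primary analysis is protected until consensus, and samples carry only their type and a study identifier. What remains is a conflict of wording.
- *All discordance handling favours cytology.* A blinded 10% review covers test-positive and test-negative cases. It serves observer agreement and does not verify disease, so it does not answer the concern, but the blanket claim is too strong.
- *Sensitivity for other pelvic cancers will approach 100% whatever the truth.* That is the limiting case a₋ = 0, and the article does not establish it.

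**Conclusion.** The concern holds as differential verification driven by the index test. For endometrial cancer the bias is upward and modest: about 0.1 to 1.9 points of sensitivity for true values of 75% to 85%. This assumes that 2 to 10 of 100 cancers are missed by the standard pathway, that half to all of the cytology-positive ones are found through triggered tests, that no cytology-negative ones are found, and that cytology performs equally in missed and found cancers.

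For the cervical, bladder and any-pelvic-cancer outcomes, sensitivity and NPV lack uniform ascertainment. The size of that bias cannot be derived from the article, but it limits what can be claimed.

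The conflict between the blinding statements needs reconciling. It has no demonstrated effect on the primary estimate.

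**What to change.** 1. Record for each cancer whether the diagnosis came through the standard pathway or through tests prompted by cytology. The flag should capture what prompted the test, because hysteroscopy is itself a pathway test.
2. Keep confirmed cancers in the primary analysis. As a sensitivity analysis, show the endometrial 2×2 table, sensitivity and NPV with and without cytology-triggered diagnoses, noting that NPV will be identical in both.
3. For non-endometrial cancers, report yield and PPV. Give sensitivity and NPV only where ascertainment is the same for cytology-positive and cytology-negative women.
4. State that the first adequate blinded consensus result is final for all accuracy estimates. A second urine used because the first was inadequate still counts. Re-reads, post hoc second urines and resamples of known false negatives are descriptive only.
5. Reconcile the absolute statement in Blinding with Sample handling and Handling of discordant results.

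Enrichment cases stay in as the protocol provides, and patient care does not change. The cost is one extra data flag and one additional table, with some sensitivity and NPV figures for other cancers possibly withheld.

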### Assessment of adverse events

Adverse events arising during the study will be recorded and managed in accordance with standard clinical practice.

### Data management and monitoring

Data will be managed by a dedicated project manager to ensure validity, accuracy and reliability. Data will be handled in accordance with Good Clinical Practice and the Data Protection Act (2018). Participants will be assigned a study-specific ID. Written, informed consent will be obtained for all participants and forms stored in local site files within locked filing cabinets. Clinical data will be collected on case report forms (CRFs) and entries verified by inspection against source data. No patient identifiers will be stored in CRFs or on the study database. A sample of CRFs (10% or as per the study risk assessment) will be checked on a regular basis for verification of all entries made. Deidentified data will be stored on a study-specific REDCap database. The capture of data on the study database will be checked and verified. Where corrections are required, these will carry a full audit trail and justification. The sponsor will periodically audit the study site file, a sample of CRFs, consent forms and source data and accuracy of the study database to ensure satisfactory completion.

### Statistical analyses

Statistical analyses will be carried out in R V.3.2.5 (R Development Core Team, Vienna, Austria) and overseen by the trial statistician. A STARD diagram depicting the flow of participants through the study will be presented. This will describe the number of participants who met the inclusion criteria but did not take part and reasons for this. Participants’ demographical and clinical characteristics at baseline will be presented by final diagnosis using appropriate descriptive statistics, mean and SD for continuous measures that are approximately symmetrical median and quartiles if the distribution is skewed. Discrete outcomes will be described using both the number and proportion (percentage). The distribution of disease will also be presented for the index test by results of the reference standard.

Analysis of the primary objective will compare the clinical performance of cytology with the reference test. Thus, sensitivity, specificity, NPV, positive predictive value and diagnostic accuracy will be reported together with their corresponding 95% CIs, calculated using the exact binomial method. Where a histology result is not available, endometrial thickness <4 mm (histology not indicated) or discharge from diagnostic workup will be used as reference standard. Analysis of the secondary objectives will assess clinical performance of the urine test alone and the vaginal test alone for the detection of endometrial cancer in relation to the reference test. The clinical performance of urine and vaginal cytology for the detection of any cancer affecting the pelvic organs will also be calculated. Secondary analyses will follow the same approach as the primary analysis. Sensitivity analyses will consider the clinical performance of cytology with a broader definition of a positive cytology result (including glandular results as test positives). Interobserver agreement between the cytopathologists will be assessed using the kappa statistic and categorised as poor, fair, moderate and good. McNemar’s χ^2^ test will be used to compare urogenital cytology with routine diagnostics. Multivariate logistic regression will evaluate the relationship between positive cytology and endometrial cancer diagnosis while adjusting for potentially predictive clinical characteristics like age and BMI. The diagnostic accuracy of urogenital cytology will be compared with individual elements of the standard diagnostic pathway, including TVS, hysteroscopy and endometrial biopsy. Consideration will be given as to where in the current diagnostic pathway for endometrial cancer urogenital cytology fits. Its use as a triage test prior to any other diagnostic workup both alone and in combination with clinical parameters (eg, age and BMI) will be modelled. We will also consider its usefulness in combination with transvaginal ultrasound scanning at various endometrial thickness cut-offs. The acceptability of urogenital sampling will be compared with transvaginal ultrasound, hysteroscopy and endometrial biopsy (online supplemental appendix 1).

10.1136/bmjopen-2021-050755.supp1Supplementary data

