### Sample size

With a sample size of ~2000 women and an endometrial cancer prevalence of 5%,^5^ there will be approximately 1900 women without endometrial cancer and 100 women with endometrial cancer. The study will have 80% power to determine the sensitivity of the test at ≥85%±7% and the specificity of the test at ≥85%±2%. At 85% specificity, around 1630 women will have a negative test result, giving the test a NPV) of 99.1% (98.5% and 99.4%). These estimates originate from the pilot study, where sensitivity and specificity were both >85%. The prevalence of endometrial cancer will determine the final sample size. If the prevalence of endometrial cancer is greater than 5%, fewer than 2000 women will be needed; if it is less than 5%, more women will be needed to determine the sensitivity of the test at ≥85%±7%.

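### As written, McNemar's test of cytology against routine diagnostics sets the index test against essentially its own reference standard, so it tests whether false positives equal false negatives and does not compare accuracy

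*Protocol article*

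**What the plan says.** The Statistical analyses section of the protocol article first plans sensitivity, specificity, predictive values and overall accuracy with exact binomial 95% CIs. It then adds that McNemar's χ² "test will be used to compare urogenital cytology with routine diagnostics". It does not define the comparator further, and it does not say whether the test is run in all women or within groups defined by disease status.

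Other sections make the routine work-up the reference standard:

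- Primary outcome measure: "The accuracy of cytology (index test) will be defined by the results of standard endometrial cancer diagnostic tests", which the same sentence labels the reference standard.
- Reference standard: "The reference standard is histology where endometrial tissue is collected for routine diagnostic and staging purposes".
- Statistical analyses, for women without histology: "endometrial thickness <4 mm (histology not indicated) or discharge from diagnostic workup will be used as reference standard".
- Handling of discordant results: a false positive is a case "where urogenital cytology is positive but standard tests are not", and a false negative is a case "where standard tests identify endometrial cancer but urogenital cytology does not".

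Two sentences after the McNemar sentence, the article separately plans to compare the accuracy of cytology with single components of the work-up (TVS, hysteroscopy and biopsy). No test is named there.

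**The concern.** McNemar's test uses only the pairs in which two classifications of the same woman disagree. If one classification is cytology and the other is the reference standard, these pairs are by definition the false positives and the false negatives. The test then asks whether there are as many of one as of the other. The two counts come from groups of very different size, and their equality does not measure sensitivity, specificity or comparative accuracy.

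The risk lies in interpretation. A reader of the results could take a small p-value to mean that cytology performs differently from routine care, or a large one to mean that it performs as well. Neither follows. This matters for a test proposed as a rule-out tool, because McNemar's is the only hypothesis test that the article names for cytology against routine care.

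**Working it through.** **Inputs (Sample size section).** The article expects "approximately 1900 women without endometrial cancer and 100 women with endometrial cancer" and works with 85% sensitivity and 85% specificity.

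**Reproducing the plan's own figures.**

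- True positives = 0.85 × 100 = 85; false negatives (FN) = 15.
- True negatives = 0.85 × 1900 = 1615; false positives (FP) = 285.
- Test negatives = 1615 + 15 = 1630, as stated.
- Negative predictive value = 1615/1630 = 99.1%, with a Wilson 95% CI of 98.5% to 99.4%, as stated.

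The 2×2 table is therefore the one the protocol had in mind. The article gives no figure for the McNemar test itself.

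**What the test examines.** Cytology positives = TP + FP. Reference positives = TP + FN. The two are equal exactly when FP = FN. The null hypothesis is thus that the cytology-positive rate equals the cancer prevalence. At the design values these are (85 + 285)/2000 = 18.5% and 100/2000 = 5%.

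**Statistic.** Chi-square = (FP − FN)²/(FP + FN) on 1 degree of freedom, without continuity correction. With 100 cancers and 1900 non-cancers:

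| Sensitivity / specificity | FP | FN | Chi-square | p |
|---|---|---|---|---|
| 85% / 85% (design target) | 285 | 15 | 270²/300 = 243 | about 9 × 10⁻⁵⁵ |
| 100% / 85% | 285 | 0 | 285²/285 = 285 | about 6 × 10⁻⁶⁴ |
| 85% / 99.2% | 15 | 15 | 0 | 1 |
| 50% / 97.4% | 50 | 50 | 0 | 1 |
| 5% / 95% (uninformative: sensitivity = 1 − specificity) | 95 | 95 | 0 | 1 |
| 0% / 94.7% (misses every cancer) | 100 | 100 | 0 | 1 |

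Continuity correction changes 243 to 241.2 and alters nothing of substance.

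Two things follow from the table. Raising sensitivity from 85% to 100% at fixed specificity makes the result more significant. And an excellent test (85%/99.2%), a mediocre one, an uninformative one and one that finds no cancer at all share the same p-value.

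**Dependence on case mix.** Keep 85%/85% and 2000 women, and change only the prevalence. At 10%, the upper end of the range in the Introduction, FP = 0.15 × 1800 = 270 and FN = 0.15 × 200 = 30, so chi-square = 240²/300 = 192. At 50%, an illustrative extreme, both counts are 150 and chi-square is 0. The Blinding section allows the cohort to be enriched with cancers if the proportion is below 5% at midpoint, so recruitment policy could move this statistic while sensitivity and specificity stayed the same.

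**The case against.** **The sentence may mean something else.** For the primary analysis the article speaks of the reference test or reference standard, but here it says routine diagnostics. The nearby comparison with TVS, hysteroscopy and biopsy has no named method, and McNemar's is the usual paired test for it. On that reading only the comparator and the strata are unstated, and a condensed article may leave such detail to a fuller document. This is a fair doubt about intent, but it does not rescue the text. The component comparison stands in its own sentence and makes no reference to McNemar's test. Run once over all women, the test would still compare positivity rates with TVS, not sensitivity or specificity.

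**Routine diagnostics and the reference standard are not identical.** A hysterectomy specimen can replace the biopsy, and a cancer found within 3 months of discharge counts as positive. The initial work-up can therefore be wrong against the final reference. This stands, and it is why the overlap is described as essential and not complete. The Handling of discordant results section nevertheless defines false results by disagreement with the standard tests.

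**Stronger readings that do not hold.** A reader might infer that low prevalence alone predetermines the p-value. It does not: the table gives both p = 1 and p near zero at the same 5% prevalence, so the result depends on prevalence, sensitivity and specificity together. A reader might also infer that the main conclusions are at risk. They are not: the primary outcome is sensitivity and specificity with exact intervals, and a test that missed every cancer would be reported there with 0% sensitivity. Nor do the documents attach any interpretation to the p-value, so misreading is a risk and not a certainty.

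**Conclusion.** The point holds as an error in a secondary analysis. As written, the McNemar test has the null hypothesis FP = FN. At the protocol's own design values that is 285 against 15 (chi-square 243), while an uninformative 5%/95% test gives 95 against 95 (chi-square 0, p = 1). The p-value cannot rank tests by accuracy or show that cytology is better than, worse than or equivalent to routine care.

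The conclusion rests on reading routine diagnostics as the complete work-up that forms the reference standard, which is the plain reading. On the alternative reading, single components, the sentence still needs a named comparator and separate analyses by disease status. The figures assume 100 cancers, 1900 non-cancers and the stated target accuracy. The qualitative conclusion does not depend on them or on the significance level, which is not stated for this test.

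The practical effect is limited. The primary estimates, their intervals and the sample size do not use this test, and no stated decision rule depends on it. It should be corrected before analysis but does not threaten the study's main result.

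**What to change.** Drop McNemar's test against the composite reference standard and reword the sentence so that it supplies the method for the component comparison already planned. Suggested wording:

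*Cytology will be compared with a named comparator test, such as TVS at a stated endometrial thickness cut-off, using McNemar's test or paired differences with 95% CIs, separately in women with endometrial cancer (sensitivity) and in women without (specificity).*

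Add a caution that some of these comparisons are partly circular. Biopsy histology is itself part of the reference standard, and TVS below 4 mm serves as the reference where no histology exists, so both comparators are favoured by construction.

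A paired comparison of urine with vaginal cytology, in the same two groups, could use the same method. It is optional, because the article plans only separate estimates for each sample type.

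The cost is one or two sentences in the analysis section. No new data, participants or procedures are needed.
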